#### Statistical Analysis

For study phase 2, we will use a multilevel model for the main outcome analysis where the participant is defined at the highest level of the model (level 2), and observations (level 1) are nested within the participant. We will assume that the observation-level (level 1) residual error term and participant-level (level 2) intercept coefficients (ie, random effects) are each normally distributed with mean zero and a variance that is estimated from the data, while intercept and slope coefficients are multivariate normally distributed with mean zero for each, and a covariance matrix that is estimated from the data. Intervention groups will be tested as a fixed effect. Given that many outcomes of our interest are count outcomes with excessive zeros, we will utilize appropriate models to accommodate a zero-inflated outcome distribution with overdispersion [44,84]. The 2 sites can be entered as a random effect (level 3) or a fixed effect in a 2-level model. We will include an interaction term to test whether PFI+CDF is similarly effective for men and women. The intercept and growth slopes will be appropriately specified to maximize information.

We will use a parallel process growth model to test the codevelopment of correlated processes (eg, alcohol use and RSB) and a parallel process growth mediation model. This allows for the examination of 2 potentially dependent reduction trajectories, which are altered by intervention. We expect that those who reduce alcohol misuse more rapidly in response to intervention will also exhibit a trajectory in which one’s likelihood of engaging in RSB decreases, which can be tested by comparing a model where the 2 slope terms are correlated with a null model where its correlation is constrained to be zero. Intervention effects can be explicitly tested by adding intervention membership as an external covariate that changes these coupled processes. Intervention effect modifiers or moderators will be tested in a confirmatory (eg, sex) or exploratory investigations.

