#### Recruitment

Contact information for a random sample of first-year college students between the ages of 18-20 years will be drawn from the registrar’s office at each study site. Students will be sent a prenotification letter on the university letterhead describing the study and inviting their participation. The letter will inform them to check their email on the study start date for more details and be followed by an email that reiterates study details, invites their participation, and includes a web link and personal identification number to access a web-based consent form and screening survey. Other recruitment methods will supplement this recruitment from the registrar’s office, including direct emails to interested students, advertisements in newspapers, on websites and social media, and postcards and fliers distributed at various on-campus locations. Eligibility criteria are shown in Textbox 1. Eligible students will be required to give informed consent before being directed to the baseline survey. Those who decline to consent and those who are not eligible will be directed out of the survey and removed from the participant list. Students will receive email reminders over the course of the following week. We will oversample underrepresented groups (n=300, 50% non-White and n=300, 50% White students) and maintain an equal ratio of men and women at each site.

Eligibility criteria for the randomized controlled trial.

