#### Sample Size Justification

Power analyses to detect intervention main effects were conducted using Optimal Design Plus Version 3.01 software and the “power determination approach.” Based on past research, we assumed a standardized effect size of 0.3 (a small to medium effect size) from the repeated measures RCT with 5 follow-ups over 13 months. To examine the effect of the PFI+CDF and PFI interventions, compared to the control, a minimum of 452 participants are required for a power of 0.8 at an alpha level of .05. To examine the effect of the PFI+CDF intervention (vs PFI+GHI or PFI-only intervention), at least 350 participants are required. Based on this power analysis, there is sufficient power (≥0.89) to detect a small to medium effect size for the integrated interventions (PFI+CDF, PFI+GHI, and PFI only) versus control and sufficient power to detect the small effect of the PFI+CDF intervention compared to the PFI+GHI or PFI-only intervention over time. Although the overall effect size was conservatively assumed to fall between small and medium in size, due to the fine-grained assessment approach within the time period where most changes are likely to occur, followed by a long-term 13-month follow-up assessment, we anticipate that the proposed study is sufficiently powered.

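### The group-by-sex interaction is meant to show that PFI+CDF works similarly in men and women, but non-significance cannot show this, and the sample was sized for main effects only

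*Protocol article*

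**What the plan says.** The Statistical Analysis section for phase 2 states: "We will include an interaction term to test whether PFI+CDF is similarly effective for men and women". The same section ends its account of moderators with: "Intervention effect modifiers or moderators will be tested in a confirmatory (eg, sex) or exploratory investigations". Sex is therefore the named example on the confirmatory side.

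The Sample Size Justification limits itself to main effects: "Power analyses to detect intervention main effects were conducted using Optimal Design Plus Version 3.01 software". It assumes a standardized effect of 0.3 and gives two sample sizes. For PFI+CDF and PFI against control, "a minimum of 452 participants are required for a power of 0.8 at an alpha level of .05". For PFI+CDF against PFI+GHI or PFI-only, "at least 350 participants are required". It also says that "there is sufficient power (≥0.89) to detect a small to medium effect size for the integrated interventions" against control.

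The Recruitment section says the study will "maintain an equal ratio of men and women at each site". The article gives no interaction effect size and no power for the interaction. It does not name the comparator for the sex interaction or say how a non-significant result will be read.

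**The concern.** The question is about similarity and the tool is a test of difference. Rejecting the null would show that the sexes differ. Failing to reject would show only that the data did not separate them. As worded, non-significance is the only outcome of this test that could be taken to mean similar effectiveness, and the confirmatory label gives that outcome weight.

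An interaction is also estimated much less precisely than the main effect for which the trial was sized. A non-significant interaction could therefore easily sit alongside a benefit confined to one sex. The risk is a published statement that an alcohol and sexual-risk program works equally well for men and women when the data could not tell.

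**Working it through.** **Inputs from the article.** Standardized effect 0.3 (so SD = 1), alpha .05 and power 0.8 (Sample Size Justification); 600 students in 4 groups (Overview of RCT Design); equal numbers of men and women (Recruitment); 5 follow-ups (Sample Size Justification).

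**Assumptions.** Two-sided test; equal allocation, so 150 per arm and about 75 per arm-by-sex cell; no dropout. The article gives no within-person or baseline correlation, so these are varied below.

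**Reproducing the plan's figures.**
- Two equal groups: total = 4 × ((1.96 + 0.842)/0.3)² = 348.8, or 175 per group and 350 in total. This matches the stated 350.
- Three PFI arms against control, 450 vs 150, d = 0.3: power 0.889, matching the stated 0.89.
- The stated 452 is not matched exactly. The same formula at 1:3 gives 465 before rounding, 2.9% higher.

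The 350 and 0.89 therefore correspond to a plain two-group comparison, with no visible gain from repeated measures.

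**Interaction, PFI+CDF against one arm.**
- SE of the arm contrast = √(1/150 + 1/150) = 0.1155.
- SE of the interaction = √(4 × 1/75) = 0.231, twice as large.
- 95% CI half-width = 1.96 × 0.231 = 0.45 SD.
- Difference detectable with 80% power = 2.802 × 0.231 = 0.65 SD.
- Effects of 0.3 and 0: 0.3/0.231 = 1.30; power = Φ(1.30 − 1.96) + Φ(−1.30 − 1.96) = 0.255; miss rate 74.5%.
- Effects of 0.6 and 0 (an average of 0.3 arising wholly in one sex): 0.6/0.231 = 2.60; power 0.738; miss rate 26%.

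**Other comparators, effects 0.3 and 0.** Two arms pooled (300): SE 0.200, miss rate 67.7%. Three arms pooled (450): SE 0.189, miss rate 64.4%. Assumed dropout of 10% or 20% raises the one-arm figure to 76.6% or 78.7%.

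**Using the repeated measures.** If r is the correlation between any two occasions, the mean of five follow-ups has variance (1 + 4r)/5. Adjusting for baseline as well gives (1 + 4r)/5 − r². Miss rates for effects of 0.3 and 0:

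| r | Averaged, vs one arm | Plus baseline, vs one arm | Averaged, vs three arms | Plus baseline, vs three arms |
|---|---|---|---|---|
| 0.3 | 50% | 41% | 33% | 23% |
| 0.4 | 56% | 42% | 40% | 25% |
| 0.5 | 61% | 41% | 46% | 23% |
| 0.6 | 65% | 37% | 51% | 20% |
| 0.7 | 68% | 30% | 55% | 13.5% |
| 0.8 | 71% | 17% | 59% | 5.5% |

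With baseline adjustment and one comparator arm, the half-width falls from 0.45 to between 0.45 × √0.36 = 0.27 (r = 0.4) and 0.45 × √0.20 = 0.20 (r = 0.8).

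**The case against.** The case for the plan has four parts.

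- **Shorthand.** Testing whether an effect is similar across sexes is a common way to describe a moderation test, and a group-by-sex interaction is the usual tool. A reader might infer that the plan commits to declaring similarity when the interaction is non-significant. The article does not say so; the inference rests on its wording and the confirmatory label. Interpretation rules can also sit in an SAP that is not shown, so the lack of a margin is not itself a fault. What remains is that the sentence as written gives a similarity question to a test that cannot answer it.

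- **The 75% is an unfavourable case.** The planned analysis is a multilevel model on repeated observations, not one unadjusted value per student. A reader might infer that the miss rate is about 75%, or at least above 20%, however the data are analysed. Neither is supported: with baseline adjustment and pooled comparators it drops below 20% at high r. Nor does the CI half-width always exceed the assumed effect.

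- **Which effect is split.** The stated 0.3 is an effect over all participants. If that average came entirely from one sex, the effects would be 0.6 and 0 and the miss rate 26%. With 0.3 and 0 the average is 0.15, and power for the main effect against one arm is itself only about 25% (0.15/0.1155 = 1.30). A claim of overall effectiveness against that arm would then be unlikely, so a false claim of equal benefit is a possible outcome, not the expected one.

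- **Aims.** A reader might tie this to the second aim, on scale-up. That aim is served by qualitative work and does not rest on the sex interaction.

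The first three arguments limit the size of the problem. None makes a non-significant interaction evidence of similarity.

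**Conclusion.** The point holds as a mismatch between the question and the test. A non-significant interaction cannot show that PFI+CDF works similarly in men and women, whatever its power, and the trial was sized for main effects only.

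How often a one-sex benefit would be missed depends on assumptions the article does not settle. For effects of 0.3 and 0 against one arm, the rate is about 75% on the basis behind the stated 350 and 0.89, about 50% to 71% with follow-ups averaged, and about 17% to 42% with baseline adjustment too (r from 0.3 to 0.8). Pooling all comparators with r of 0.7 or more, and adjusting for baseline, brings it to 14% or less. All figures assume equal allocation, an even sex split and a standardized scale, which only approximates the zero-inflated count models planned.

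This is a secondary analysis, but an unsound conclusion is foreseeable and cheap to prevent.

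**What to change.** Keep the model and the group-by-sex interaction, and change the stated purpose and reporting:

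- Report the PFI+CDF effect in men, the effect in women, and the difference between them (for count outcomes, the ratio of rate ratios), each with a 95% CI.
- State that a non-significant interaction will not be taken as evidence of similar effectiveness.
- State that the sample was sized for main effects, so the sex comparison is supportive.

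No equivalence margin is needed. On the unadjusted basis a 95% CI with a half-width of 0.45 SD could never lie inside a margin below 0.3 SD, so such a rule could not be met.

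The cost is a few sentences; data, model and sample size are unchanged. The small downside is that the sex result may have to be reported as inconclusive.

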### Implementation (Phase 3)

A qualitative postintervention assessment of intervention implementation will be conducted with multilevel stakeholders, including students and both campus- and national-level student affairs staff. The goals are to better understand (1) participating students’ experiences with the intervention; (2) barriers and facilitators to implementation, guided by CFIR; (3) potential program sustainability; and (4) necessary modifications for other sites for scale-up.

Focus group participants will be a subset of students from the PFI+CDF arm of the RCT, as well as campus- and national-level stakeholders who also participated in preimplementation focus groups. Participants in the PFI+CDF condition will be asked if they are interested in participating in a follow-up study after the 13-month follow-up. We will randomly select up to 48 students who indicate interest in participating (n=24 per site) at varying levels of engagement with the intervention (as guided by program analytic measures) for a maximum of 3 focus groups per site (5-8 participants per group). Campus student affairs staff will be contacted via phone and email for staff focus groups (1 focus group per site for student affairs staff with 5-8 participants per group). At the national level, we will conduct 4 focus groups, with 5-8 participants per group, yielding a total of up to 32 participants. All focus groups will last 60-90 minutes with US $50 and US $100 gift card incentives for students and staff, respectively. The analytic plan for phase 3 qualitative data will mirror phase 1.

### Ethics Approval

The study underwent review and approval by the UK Institutional Review Board (IRB #62769), which serves as the single IRB of record for this study. All participants will sign an approved consent form in accordance with the ethical standards of Helsinki.

## Results

Recruitment and enrollment for phase 1 began in January 2022. The findings of phase 1 will inform the development and build of integrated PFI+CDF. It is anticipated that phase 2 will begin in August 2023, and phase 3 will begin in October 2024. Data will be shared in the NIAAA Data Archive twice a year (April 1 and October 1), starting from October 1, 2023. Findings will be published in peer-reviewed journals and presented at international, national, or regional professional meetings and conferences.

## Discussion

### Overview

This project aims to fill a gap highlighted in the NIAAA Strategic Plan 2017-2021 [3] by advancing an intervention that integrates alcohol misuse and RSB. It also directly addresses the 2 primary areas of foci underlying a recent NIAAA workshop to advance the science on evidence-based brief interventions for young adult populations: (1) optimizing intervention design and (2) implementation and scale-up [85]. To the best of our knowledge, the use of dynamic feedback based on individual behavior trajectories to optimize PFI content with rapid and sustained deliveries and ongoing evaluations has never been attempted with this population and area of study. Understanding the impact of a dual-risk behavior PFI that incorporates novel, cross-tailored between- and within-person feedback profiles can help inform best practices for the delivery of prevention interventions relevant to college students. If successful, our approach could influence how PFIs are developed and delivered in other populations and settings for maximum benefit. In addition, employment of a hybrid type 1 effectiveness-implementation design for this population, behavior, and campus setting is also the first of its kind and is expected to yield broadly informative outcomes through its rigorous randomized trial design testing intervention effectiveness and multilevel stakeholder engagement pre- and postimplementation.

### Limitations

There are several potential limitations that need to be acknowledged. First, the emphasis on first-year college students may be restrictive. We chose to focus on first-year students because they are at risk for alcohol use and RSB [16-26], but older students also experience alcohol-related harms. Many college campuses require students to complete a brief alcohol intervention at the start of college and often use existing commercialized PFIs, providing a built-in audience for the adapted PFI+CDF intervention [35,36]. We encourage future studies to explore PFI+CDF in other at-risk populations, such as older students and young adults not in college. Second, the PFI+CDF intervention approach is intensive and could lead to concerns about student engagement. However, our past work on integrated PFIs indicates that participants engaged with feedback content and viewed it multiple times [86]. We demonstrated that increased personalization leads to a stronger program effect, potentially mediated through increased attention to content [32]. By involving students in the design process in phase 1, we should enhance their interest [59,87,88]. Students also reported favorable reactions to the proposed study methods. Thus, we anticipate high levels of engagement, but will also examine program engagement in phase 2 analyses and phase 3 focus groups. Third, there are alternatives to a web-based app platform. Technology changes rapidly, with many other options for content delivery (eg, native mobile apps, smartwatches, social media). Our goal was to create a flexible system to deliver content in multiple ways (email and SMS text message), increasing the likelihood of engagement. Native mobile apps require more programming than web apps to operate across smartphone types and operating systems. Social media offers opportunities (eg, user-generated interaction and content) but also its own challenges (eg, spread of misinformation). Alternate delivery platforms will be explored during focus groups, and we anticipate the need for content to be portable to other platforms in future implementation.

### Conclusions

This innovative, multisite hybrid effectiveness-implementation study will (1) evaluate the impact of a PFI that integrates content on alcohol use and RSB and is adapted to include an innovative CDF component for at-risk first-year college students and (2) identify implementation factors critical to its success to facilitate future scale-up in campus settings. The findings of this study will improve existing evidence-based alcohol programs and bridge the gap between research and practice at the university level.

## Appendix

Multimedia Appendix 1 Peer-reviewer report from the Interventions to Prevent and Treat Addictions Study Section - Risk, Prevention and Health Behavior Integrated Review Group (National Institutes of Health, USA).

## Abbreviations

AOC: assessment-only control
CDF: cross-tailored dynamic feedback
CFIR: Consolidated Framework for Implementation Research
GHI: generic health information
IRB: Institutional Review Board
NIAAA: National Institute on Alcohol Abuse and Alcoholism
PFI: personalized feedback intervention
RCT: randomized controlled trial
RSB: risky sexual behavior
UK: University of Kentucky
UNT: University of North Texas
